#### Procedure

After basic demographic data (age, gender, education) and individual prior experiences with Parkinson disease have been collected, the study participants will be asked to put themselves in the position of a patient with idiopathic Parkinson disease with the help of a case description. The following dependent variables will be measured as target variables before and after the use of the decision support: decisional conflict [38]; hypothetical decision (which treatment option would be preferred); attitude toward both treatment options (modified according to [39]); and knowledge about risks and side effects of treatment options, mode of action of treatment options, and possible advantages and disadvantages of treatment options.

Subsequently, participants will be randomly assigned (computer-generated assignments) to the 3 conditions. Based on the results of Study 1a and Study 1b, a text- and video-based decision aid will be designed with a maximum reception time of 15 minutes.

In addition, the following are to be completed after the decision aid has been used: preparation for decision making (based on [40]); evaluation of the preferences or motives identified in Study 1 with regard to the importance for the decision made, decision evaluation scale [41]; reflection on one’s own reasons for the decision; suggestions for improvement (open answer format), and the knowledge test.

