### Study 2: Effects of Decision Aids on the Decision-Making Process (People With Nonmedical Background)

#### Study Design

Based on the patient preferences identified in Study 1, online decision aids will be designed in close collaboration with health professionals. We will use a participatory design process to increase the later acceptance and use of the decision aids, and thus, facilitate the implementation process in clinical practice. The impact of the decision aids on the decision-making process will be investigated in a randomized controlled trial with a 1×3 between-subject design with the following 3 groups: condition 1, decision aid with factual information (control); condition 2, decision aid with factual information and patient reports on the individual motives underlying the decision-making process; and condition 3, decision aid with factual information and patient reports on the outcomes achieved through the treatment option.

In condition 3, positive and negative outcomes will be presented according to the actual success rate of the treatment options, that is, both successful and less successful treatment outcomes will be shown for both treatment options. The information provided to the participants regarding the success rates of the treatment options will be based upon existing literature in line with institutional history.

We hypothesize that the conditions containing patient reports on motives or outcomes will have a beneficial effect compared to the condition with only factual information; participants to whom decision aids with patient reports are presented will feel better prepared for decision making (Hypothesis 1) and will evaluate the decision more positively (Hypothesis 2). It is an open research question whether the two conditions with patient reports on individual motives and patient reports on outcomes will also differ with respect to preparation for decision making and decision evaluation.

In addition, this study will be used to evaluate and refine the factual information part of the decision aid. Participant knowledge about treatment options will be evaluated pre and posttest to identify which facts are difficult to understand (and which, perhaps, even result in misunderstandings or irrational fears). This information will influence the design of the factual information and will be re-evaluated in the subsequent study (Study 3).

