#### Measures

A pre-existing decisional conflict questionnaire will be used [38]. Participants will be asked, “How sure are you about your decision for surgical or non-surgical treatment?” and will reply to three statements using a 7-point Likert scale for each: “It's hard for me to make that decision”; “I'm not sure how to act on this decision”; “It's clear which choice is best for me.” They will also be asked “How do you feel about this decision?” and reply to 4 statements using a 7-point Likert scale: “I feel like I made an informed decision”; “My decision shows what is most important to me”; “I expect to stick to my decision”; “I'm satisfied with my decision.” Attitude toward both treatment options will be measured with a 4-item scale (modified following [39]; Figure 1). The knowledge test will be based on the results of Study 1b. The aim will be to provide information on any existing misconceptions or false information regarding the treatment options for Parkinson disease and to test the efficacy of the information provided (a maximum of 10 items). The postintervention preparation for decision making scale is based on [40] (Figure 2). The numerical scale has treatment options ranging from deep brain stimulation on one end of the scale to pure drug therapy on the other end. A decisional conflict questionnaire [38], ratings of feelings about the decision, ratings of attitude toward both treatment options [39], and the decision evaluation scale [41] (Figure 3) will be used.

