**Figure 3 figure3:**
[figure not shown]
Decision evaluation scale.

A maximum of 16 items will be used to evaluate the preferences and motives that were identified in Study 1 with regard to the importance for the decision made such as (the following items are example items only since the items are not yet known): “Please rate the extent to which you agree with the following statements. There is no right or wrong answer. We are only interested in your personal opinion and assessment.”; “The very small, but existing danger of an irreversible side effect (eg, by a brain hemorrhage) with the deep brain stimulation, influenced my decision strongly.”; “The hope for improvement of my independence in everyday life, through deep brain stimulation, has strongly influenced my decision.”; “The concern about psychological impairment (eg, psychosis, states of confusion) in a pure drug treatment had a strong influence on my decision.”

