#### Procedure

Basic demographic data (age, sex, education) and the individual perception of the limitations caused by the disease will be collected with the PDQ-39 [34]. Participants will be asked to complete the following questionnaires before and after the use of the decision support: decisional conflict [38]; hypothetical decision (“which treatment option would you probably choose in this situation?”); attitude toward both treatment options (modified following [39]); study-designed knowledge test on risks and side effects of treatment options, mode of action of treatment options, possible advantages and disadvantages of treatment options questionnaires will be used. In addition, the following will be completed after the decision aid has been used: preparation for decision making (based on [40]); evaluation of the preferences and motives identified in Study 1 with regard to the importance for the decision made; decision evaluation scale (based on [41]; reflection on one’s own reasons for the decision; suggestions for improvement (open answer format).

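### The order of the motive ratings and the decision evaluation scale is not fixed, and the order the Procedures list would prompt every arm with the motives before the Hypothesis 2 outcome

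*Protocol article*

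**What the plan says.** **Study 2, Procedure.** The lead-in reads "the following are to be completed after the decision aid has been used: preparation for decision making". The list continues with "evaluation of the preferences or motives identified in Study 1 with regard to the importance for the decision made, decision evaluation scale", then reflection on one's reasons, suggestions for improvement and the knowledge test.

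**Study 3, Procedure.** The same neighbours appear in the same order: "evaluation of the preferences and motives identified in Study 1 with regard to the importance for the decision made; decision evaluation scale".

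**Study 2, Measures.** The decision evaluation scale comes before the motive items. The text first says "and the decision evaluation scale [41] (Figure 3) will be used", and the motive items follow Figure 3: "A maximum of 16 items will be used to evaluate the preferences and motives that were identified in Study 1". One example item is "The hope for improvement of my independence in everyday life, through deep brain stimulation, has strongly influenced my decision". No arm is exempted. Study 3 Measures carries all Study 2 scales over.

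**Study 2, Study Design.** The control aid holds factual information only. The motive arm is "condition 2, decision aid with factual information and patient reports on the individual motives underlying the decision-making process", and the third arm adds patient reports on outcomes. Hypothesis 2 is that the report arms evaluate the decision more positively. Whether the two report arms differ is an open question.

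**The concern.** The arms differ in whether motives or outcomes are put before the participant, and the Goals section asks whether presenting possible preferences helps decision making. The motive items also present preferences: each names a motive and asks the participant to weigh it against the decision just made. If they come before the decision evaluation scale, the control and outcome-report arms have been prompted with the motives featured in condition 2 by the time the Hypothesis 2 outcome is taken.

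Two Study 2 comparisons could be blurred: report arms against control (Hypothesis 2), and motives against outcomes. Study 2 also guides the choice of format for Study 3, where the same listed order recurs. There the issue matters mainly if the motives format is the one selected. Such exposure cannot be undone after data collection.

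**Working it through.** **1. The orders side by side**

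| Place | Listed first | Listed second |
|---|---|---|
| Study 2, Procedure | motive ratings | decision evaluation scale |
| Study 3, Procedure | motive ratings | decision evaluation scale |
| Study 2, Measures | decision evaluation scale | motive items |

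Nothing states that any of these is the order of administration. The lead-ins fix only that the instruments follow the aid. The preparation scale (Hypothesis 1) stands before the motive ratings in both Procedures, so Hypothesis 1 is untouched under that order.

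**2. The plan's own figure**

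Study 2 plans 37 per condition (N = 111) for f = 0.30, alpha 0.05 and power 0.90, using a repeated-measures ANOVA with a between-subject factor. Assuming two measurements and a correlation of 0.5 (neither is stated):

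- λ = f²·N·m / (1 + (m − 1)ρ) = 0.09 × 111 × 2 / 1.5 = 13.32
- df = (2, 108), power = 0.907

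The stated size reproduces. The point is about order and does not change it.

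**3. Illustration of what exposure could do to Hypothesis 2**

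The documents give no size for the exposure effect. Everything below is assumption.

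- Suppose both report arms exceed control by the same d. The arm means are 0, d, d, so f = d·√2/3 and d = 0.30 × 3/√2 = 0.636.
- Pooled contrast, report arms against control: SE = √(1/37 + 1/74) = √(1.5/37) = 0.2013 in SD units. The two-sided critical t with 108 df is 1.982.
- No exposure effect: ncp = 0.636/0.2013 = 3.16, power 0.88.

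Let a share s of d pass to participants who read the items. Condition 2 has already met the motives in its aid and is assumed to gain nothing.

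- *Control alone gains:* contrast = d(1 − s).
- *Control and condition 3 both gain:* contrast = (d + d + s·d)/2 − s·d = d(1 − s/2).

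| s | Control alone: d, power | Control and condition 3: d, power |
|---|---|---|
| 0.10 | 0.573, 0.80 | 0.605, 0.85 |
| 0.25 | 0.477, 0.65 | 0.557, 0.78 |
| 0.50 | 0.318, 0.35 | 0.477, 0.65 |

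The second case fits the text better, because every arm completes the items. It also shifts the motives-against-outcomes difference by s·d against the motives arm: 0.25 × 0.636 = 0.159 at s = 0.25.

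**4. Study 3**

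With 36 per arm and d = 0.70, a two-sided t test at 0.05 has power 0.834. If the contrast shrank by a quarter (d = 0.525), power would be 0.594. Two-sided testing is an assumption.

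**The case against.** The strongest reply is that a list is not a sequence. The lead-in fixes only that the instruments follow the aid, and the Study 2 Procedure is not a strict timeline elsewhere: it mentions before-and-after measurement ahead of random assignment, and it names knowledge twice. The differing order in Measures may then mean only that list order carries no timing. An article may also leave page order to the questionnaire script, and the motive items were not yet known.

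This stands against two inferences a reader might draw:

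- *That the control arm will be shown the motives before the scale.* The text supports this only conditionally, if the Procedure list is the running order.
- *That the control arm would receive the content of condition 2.* That content is patient reports within a text- and video-based aid. The items are short rating statements, and two of the three examples concern treatment risks that the factual information may already cover.

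The direction is also likely rather than shown. Facts-only participants confronted with motives they had not considered might rate their decision lower, which would widen the contrast. The quarter share has no source.

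The reply does not remove the point. The Procedures are where a reader looks for the running order, both give the same one, and it places motive prompts before a hypothesis outcome in every arm.

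**Conclusion.** The point holds in conditional form, as a minor improvement that costs almost nothing. The article lists the motive ratings before the decision evaluation scale in both Procedures and after it in Measures, and does not say which order applies. Run as the Procedures list them, the ratings would prompt all arms with the motives before the Hypothesis 2 outcome. That could blur Hypothesis 2 and the comparison of motives with outcomes, probably toward no difference, and Study 3 mainly if the motives format is chosen.

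The size cannot be estimated from the documents. The power figures in the working show only how sensitive the contrast is. They rest on equal effects in both report arms, an assumed share passed on, and no gain in condition 2. A definite loss of power, or a contaminated control arm as established fact, would be more than the documents support.

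**What to change.** State one order of administration in both Procedure sections and align Measures with it. After the aid, the decision evaluation scale and the other post-aid outcome measures (preparation for decision making, decisional conflict, hypothetical decision, attitudes and the knowledge test) are completed first. The motive ratings follow, together with the reasons and suggestions at the end.

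The cost is a reordering of online pages and a sentence in each Procedure. Arms, instruments and sample sizes stay as they are. It must be done before data collection in each trial.

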#### Measures

A pre-existing decisional conflict questionnaire will be used [38]. Participants will be asked, “How sure are you about your decision for surgical or non-surgical treatment?” and will reply to three statements using a 7-point Likert scale for each: “It's hard for me to make that decision”; “I'm not sure how to act on this decision”; “It's clear which choice is best for me.” They will also be asked “How do you feel about this decision?” and reply to 4 statements using a 7-point Likert scale: “I feel like I made an informed decision”; “My decision shows what is most important to me”; “I expect to stick to my decision”; “I'm satisfied with my decision.” Attitude toward both treatment options will be measured with a 4-item scale (modified following [39]; Figure 1). The knowledge test will be based on the results of Study 1b. The aim will be to provide information on any existing misconceptions or false information regarding the treatment options for Parkinson disease and to test the efficacy of the information provided (a maximum of 10 items). The postintervention preparation for decision making scale is based on [40] (Figure 2). The numerical scale has treatment options ranging from deep brain stimulation on one end of the scale to pure drug therapy on the other end. A decisional conflict questionnaire [38], ratings of feelings about the decision, ratings of attitude toward both treatment options [39], and the decision evaluation scale [41] (Figure 3) will be used.

**Figure 1 figure1:**
[figure not shown]
Attitude toward treatment options.

**Figure 2 figure2:**
[figure not shown]
Preparation for decision making scale.

**Figure 3 figure3:**
[figure not shown]
Decision evaluation scale.

A maximum of 16 items will be used to evaluate the preferences and motives that were identified in Study 1 with regard to the importance for the decision made such as (the following items are example items only since the items are not yet known): “Please rate the extent to which you agree with the following statements. There is no right or wrong answer. We are only interested in your personal opinion and assessment.”; “The very small, but existing danger of an irreversible side effect (eg, by a brain hemorrhage) with the deep brain stimulation, influenced my decision strongly.”; “The hope for improvement of my independence in everyday life, through deep brain stimulation, has strongly influenced my decision.”; “The concern about psychological impairment (eg, psychosis, states of confusion) in a pure drug treatment had a strong influence on my decision.”

#### Analysis

Data analysis will be performed using SPSS statistical software (version 25; IBM Corp) . We will perform an analysis of variance with posthoc tests (for interval-scaled data) and Mann-Whitney tests (for ordinal-scaled data). We will report all data as means and standard deviations (for interval-scaled data) and the median (for ordinal-scaled data). The level of significance will be set at *P*<.05. Cohen *d* and *r* will be calculated as effect sizes.

### Study 3: Effects of Decision Aids on the Decision-Making Process (Patients With Parkinson Syndrome)

#### Study Design

Based on the decision aids examined in Study 2, the most suitable format for a preference-sensitive decision will be selected and its efficacy will be compared with that of the use of pure factual information. If the need for further modifications of the decision aids becomes apparent in Study 2, we will implement the modifications in collaboration with health professionals. All of the participating patients will be given the opportunity to use the information material of the other condition immediately after the data collection. This ensures that none of the study participants will have any disadvantages, despite the randomized between-subject design.

#### Participants

Recruitment will be carried out with the support of the special outpatient units of the University Hospital Tübingen, neurologists in private practices, and Parkinson self-help groups. The same inclusion and exclusion criteria used in Studies 1a and 1b will be used for Study 3. Since, in this case, only medium to large effect strengths (*d*=.70) have clinical relevance, a sample size of 36 participants per condition will be targeted.

#### Procedure

Basic demographic data (age, sex, education) and the individual perception of the limitations caused by the disease will be collected with the PDQ-39 [34]. Participants will be asked to complete the following questionnaires before and after the use of the decision support: decisional conflict [38]; hypothetical decision (“which treatment option would you probably choose in this situation?”); attitude toward both treatment options (modified following [39]); study-designed knowledge test on risks and side effects of treatment options, mode of action of treatment options, possible advantages and disadvantages of treatment options questionnaires will be used. In addition, the following will be completed after the decision aid has been used: preparation for decision making (based on [40]); evaluation of the preferences and motives identified in Study 1 with regard to the importance for the decision made; decision evaluation scale (based on [41]; reflection on one’s own reasons for the decision; suggestions for improvement (open answer format).

#### Measures

Personal assessment of the current stage and burden of the disease will be measured using the validated questionnaire PDQ-39 [28]. Moreover, the German version of the Apathy Evaluation Scale [35] and the German version of the short-scale for assessing the personality traits in the five-factor model (big five) [36] will be used. In addition, all of the scales in Study 2 will be used. Differences will be only in the introduction to the topic (in Study 3 the participants are patients who are actually affected) and the study design. At the end of the study, the participants will also be given the opportunity to use the information material of the other condition.

#### Analysis

Data analysis will be performed using SPSS statistical software (version 25.0; IBM Corp). We will perform *t* tests (for interval-scaled data) and Mann-Whitney tests (for ordinal-scaled data). We will report all data as means and standard deviations (for interval-scaled data) and as the median (for ordinal-scaled data). The level of significance will be set at *P*<.05. Cohen *d* and *r* will be calculated as effect sizes.

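### Study 2 names one set of outcomes as targets and puts its hypotheses on another; Study 3 compares efficacy without naming any outcome

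*Protocol article*

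**What the plan says.** Four places in the protocol article bear on this point.

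- **Study 2, Study Design.** The hypotheses are that participants who see patient reports "will feel better prepared for decision making (Hypothesis 1) and will evaluate the decision more positively (Hypothesis 2").
- **Study 2, Procedure.** "The following dependent variables will be measured as target variables before and after the use of the decision support": decisional conflict, hypothetical decision, attitude toward both options, and knowledge. The two hypothesis scales are not among them. They come in a second list: "In addition, the following are to be completed after the decision aid has been used: preparation for decision making", with decision evaluation further along.
- **Study 3, Study Design, Procedure and Measures.** The selected format is to be compared for efficacy with pure factual information. No hypothesis is stated and no outcome is attached to the word efficacy. The same two lists of measures return, the second opening with "In addition, the following will be completed after the decision aid has been used: preparation for decision making (based on [40").
- **Analysis, Studies 2 and 3.** Study 2: "We will perform an analysis of variance with posthoc tests (for interval-scaled data"), with Mann-Whitney tests for ordinal data. Study 3: t tests and Mann-Whitney tests. Both sections then say "The level of significance will be set at *P*<.05". No outcome is called primary in either study.

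**The concern.** A reader who asks which result would show that the aid works gets two answers for Study 2 and none for Study 3. The measures called targets carry no hypothesis, and the measures that carry the hypotheses are not called targets.

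Study 3 is the step in patients that is meant to support an evidence-based aid for a choice between surgery and drugs, and the Discussion foresees physicians using the aid if it is shown to support shared decision making. Study 2 also decides which format goes forward. If the success outcome is open at both stages, it can be settled after the results are known, and the stated 5% level no longer describes the risk of a false claim.

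**Working it through.** **1. Which outcomes could carry a claim of benefit.** Study 3 has six main scales: the four pre/post measures, plus preparation and decision evaluation. The motive ratings are left out.

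- Attitude and hypothetical decision have no favourable direction. The Decision Aids section of the Introduction says patients should not be pushed toward either option and treats persuasion as a problem.
- Knowledge in Study 2 serves to refine the factual part, which every arm receives.
- Three measures with a plausible benefit direction remain: decisional conflict, preparation and decision evaluation.

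**2. The plan's own sample sizes.**

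*Study 2.* Inputs from Participants: f = 0.30, alpha .05, power .90, 37 per group, ANOVA with repeated measurements and between-subject factors. Assumed, because not stated: m = 2 measurements with correlation ρ = .5. The noncentrality is λ = f²·N·m/(1+(m−1)ρ) = 0.09 × 111 × 2/1.5 = 13.32. On F(2, 108) this gives power .907, and 37 is the smallest group size that reaches .90. The stated figure is reproduced.

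That model needs at least two measurements per participant, and the H1 and H2 scales have one. For a one-way ANOVA λ = 0.09 × 111 = 9.99, which gives power .803. Power .90 would need N = 144, or 48 per group (.901). So the sample size fits the target list and the hypotheses sit on the other list.

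*Study 3.* Inputs from Participants: d = .70, 36 per arm. The noncentrality is 0.70 × √(36/2) = 2.970 on 70 degrees of freedom. Two-sided at .05 (critical t 1.994) the power is .834; one-sided at .05 (critical t 1.667) it is .903. The article states neither power nor sidedness.

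**3. Chance of at least one significant result when the aid has no effect.** For k independent outcomes tested two-sided at .05 this is 1 − .95^k; counting only results that favour the aid, it is 1 − .975^k.

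- k = 3: 1 − .95³ = .143; favouring the aid only, 1 − .975³ = .073.
- k = 6: 1 − .95⁶ = .265.

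For correlated outcomes, null trials were simulated with 36 per arm, equicorrelated normal outcomes and t tests (200,000 runs per setting). The correlations are assumptions.

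| Correlation | 3 outcomes, either direction | 3 outcomes, favouring the aid | 6 outcomes, either direction |
|---|---|---|---|
| 0 | .143 | .073 | .265 |
| .3 | .136 | .069 | .242 |
| .5 | .127 | .063 | .209 |
| .7 | .109 | .054 | .166 |

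The proper yardstick for the middle column is .025, the favourable half of one two-sided test, so it runs from .054/.025 = 2.2 to .073/.025 = 2.9 times that. If testing were one-sided at .05, the favourable-only figure for three independent outcomes would be back at .143.

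**4. Study 2, within one hypothesis.** H1 sets two patient-report arms against control. Two unadjusted comparisons at .05 on that single outcome give about .09 in simulation (37 per group). Naming a primary outcome does not remove this.

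**The case against.** Much of the case on the other side stands.

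- The Study 2 Procedure can be read as sorting measures by timing, with its label for the first list not meant as primary. That makes the mismatch milder than a flat contradiction. It still leaves the hypothesis scales outside the only list given special status, and it does not help Study 3, where efficacy has no outcome at all.
- A significance level is a generic statement. It does not say that nothing will be adjusted, and multiplicity rules may stand in an analysis plan not shown here. Their absence is therefore not the point. The point is that the document gives two answers on what Study 2 is about and none on what Study 3 efficacy means.
- A reader might infer that the risk of a false efficacy claim is two to five times nominal. The documents do not support this. The upper end needs all six scales to count as evidence of benefit and to be independent, and it counts results that favour the control. Attitude and hypothetical decision have no benefit direction, and scales about one decision are likely to be correlated.
- A reader might also infer that the plan declares success on any one significant scale. It does not say so; it only fails to exclude it.
- Choosing preparation as primary is a judgement. The Goals section speaks of taking preferences into account and feeling confident, which fits decisional conflict or decision evaluation at least as well. The sponsor may choose differently, provided the choice is fixed in advance.

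**Conclusion.** The point holds as a misalignment that leaves the success outcome open. If any of the three plausible benefit measures could carry the claim, the chance of at least one two-sided significant result under no effect is about 11 to 14%, or about 5 to 7% counting only results that favour the aid. With all six scales it is about 17 to 26% in either direction, the top figure being the independence limit.

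These figures rest on assumed correlations of 0 to .7, on t tests with normal outcomes, and on the premise that one significant scale suffices, which the article permits but does not state. The mismatch itself needs no assumption. As of June 2020 only Study 1a had begun data collection, so the change could be made before any Study 2 or 3 data. It should be made, and it does not call the design into question.

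**What to change.** 1. Align the Study 2 Study Design, the Study 2 Procedure and the Study 3 Study Design. In both studies, name preparation for decision making (H1) as the primary outcome and test decision evaluation (H2) only if H1 is significant. Another single primary is acceptable if the sponsor names it before Study 2 data.
2. State in Study 3 that efficacy means the primary outcome, and state the sidedness of the test.
3. Label the remaining scales secondary or exploratory. Treat attitude and hypothetical decision as checks for unwanted persuasion.
4. In Study 2, control the two comparisons with control. For example, give each .025 (2 × .025 = .05) and test H1 before H2 within each comparison.
5. Drop the target label from the Study 2 Procedure or attach it to the hypothesis scales, and restate the Study 2 power.

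**Cost.** Secondary scales can no longer carry the efficacy claim alone. Study 3 power for the primary is unchanged at 0.83 (two-sided, d = .70, 36 per arm); splitting alpha over two outcomes at .025 each would lower it to 0.75. Study 2 does pay: for a primary measured once, the omnibus power with 111 participants at f = 0.30 is about 0.80. Keeping .90 would need 144 participants, 33 more, and the power of the adjusted comparisons with control has to be worked out separately.
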